## Abstract

**Background:**

EQ-5D is one of the most commonly used questionnaires to measure health-related quality of life. It is included in many of the Swedish National Quality Registers (NQRs). EQ-5D health states are usually summarized using “values” obtained from members of the general public, a majority of whom are healthy. However, an alternative, which remains to be studied in detail, is the potential to use patients’ self-reported overall health on the visual analog scale (VAS) as a means of capturing experience-based perspective.

**Objective:**

The aim of this study is to assess EQ VAS as a valuation method with an experience-based perspective through comparison of its performance across and within patient groups, and with that of the general population in Sweden.

**Methods:**

Data on nearly 700,000 patients from 12 NQRs covering a variety of diseases/conditions and nearly 50,000 individuals from the general population will be analyzed. The EQ-5D-3L data from the 12 registers and EQ-5D-5L data from 2 registers will be used in the analyses. Longitudinal studies of patient-reported outcomes among different patient groups will be conducted in the period from baseline to 1-year follow-up. Descriptive statistics and analyses comparing EQ-5D dimensions and observed self-assessed EQ VAS values across and within patient groups will be performed. Comparisons of the change in health state and observed EQ VAS values at 1-year follow-up will also be undertaken. Regression models will be used to assess whether EQ-5D dimensions predict observed EQ VAS values to investigate patient value sets in each patient group. These will be compared across the patient groups and with the existing Swedish experience-based VAS and time trade-off value sets obtained from the general population.

**Results:**

Data retrieval started in May 2019 and data of patients in the 12 NQRs and from the survey conducted among the general population have been retrieved. Data analysis is ongoing on the retrieved data.

**Conclusions:**

This research project will provide information on the differences across and within patient groups in terms of self-reported health status through EQ VAS and comparison with the general population. The findings of the study will contribute to the literature by exploring the potential of self-assessed EQ VAS values to develop value sets using an experience-based perspective.

**Trial Registration:**

ClinicalTrials.gov NCT04359628; https://clinicaltrials.gov/ct2/show/NCT04359628.

**International Registered Report Identifier (IRRID):**

DERR1-10.2196/27669

## Introduction

### Background

According to the US Food and Drug Administration, patient-reported outcomes (PROs) are defined as outcomes reported by patients without interpretation by anyone else [1]. They provide important information on outcomes that matter to patients [2], such as symptoms, functional outcomes, and health-related quality of life (HRQoL) [3,4]. PROs are increasingly used in health care [5,6] with applications in informing clinical practice and guidelines, informing health policy as well as supporting drug approval process among others [7]. In addition, PROs can be employed in different areas such as population surveillance, individual patient–clinician interaction, and research [8].

Patients provide information on standardized questionnaires termed patient-reported outcome measures (PROMs) [9], which are categorized into generic and disease/condition-specific PROMs. Generic PROMs enable comparisons across different patient groups and allow overall evaluation of care and quality of life. EQ-5D and the 36-item Short-Form (SF-36) are among the most common generic questionnaires. Condition-specific PROMs are used to assess outcomes specific to particular diseases/conditions from the perspective of patients [9,10].

The EQ-5D is a generic questionnaire used to measure HRQoL worldwide for a range of conditions and treatments [11]. It has a descriptive system (a set of questions in an HRQoL questionnaire encompassing different dimensions of health, the answers to which form a profile of an individual’s health) where respondents report their health in 5 dimensions (mobility, self-care, usual activities, pain/discomfort, anxiety/depression). Each of the 5 dimensions is measured with 1 question on the descriptive system of the EQ-5D questionnaire. EQ-5D contains a visual analog scale (EQ VAS) component for recording the respondent’s overall assessment of her/his health. There are 2 versions of the instrument for use in adults: one with 3 levels of severity (EQ-5D-3L) (1=no, 2=some/moderate, and 3=extreme problems/confined to bed/unable to), resulting in 243 (3^5^) unique health states. The other version with 5 levels of severity (EQ-5D-5L) (1=no, 2=slight, 3=moderate, 4=severe, and 5=extreme problems/unable to), resulting in 3125 (5^5^) unique health states. A health state is defined by combining the severity level from each of the 5 dimensions (e.g. for EQ-5D-3L health state 11223; no problem in the mobility [level 1] and self-care [level 1] dimensions, some problems with performing usual activities [level 2], moderate pain/discomfort [level 2], and extreme anxiety/depression [level 3]) [11].

An EQ-5D health state can be summarized into a single index (EQ-5D index) by applying a formula that attaches specific weights to each severity level in each dimension; this set of weights is termed a value set. The weights in a value set reflect the relative importance of the health dimensions and severity levels. The EQ-5D index enables the ranking of health states and can be used as the quality component in the adjustment of life years for calculation of quality-adjusted life years (QALYs) to be used in economic evaluation [12]. Commonly, EQ-5D indices are anchored at 1 (full health) and 0 (state as bad as being dead), with states considered worse than being dead given negative values [13].

A value set can be obtained using different health state valuation methods; for example, time trade-off (TTO), VAS, the standard gamble (SG) method, and the discrete choice experiments (DCEs) [12]. Choice-based health state valuation methods, which involve choosing between alternative scenarios, are crucial to produce health state utility used in the calculation of QALYs for use in cost-utility analyses. Such health state valuation methods are SG, TTO, and DCEs. SG is considered to have the strongest theoretical foundation on the basis of entailing the attributes of being choice based and incorporating an element of uncertainty. However, in terms of feasibility, TTO showed a better response rate [14] and is commonly employed in health state valuation. The VAS valuation method involves rating health states on the VAS scale. This leads to choice-based methods being preferred over it, as they are considered to allow choice/trade-off [15].

Currently, more than 30 countries have developed value sets for the EQ-5D-3L, predominantly using the TTO method. Some of the value sets have employed the VAS method, where respondents are asked to value described health states on the EQ-5D VAS. The EQ-5D VAS has a similar “thermometer”-like design as the EQ VAS, but when used for valuation purposes, respondents are given instructions to value a series of hypothetical EQ-5D health states by indicating where on the 0-100 line of the VAS they lie [12,13,16]. The EQ-5D-3L and EQ-5D-5L sample questionnaires containing the descriptive system and EQ VAS are presented in Multimedia Appendices 1 and 2 (Reproduced by permission of the EuroQol Research Foundation). In the development of value sets for the EQ-5D-5L, the TTO method is currently used together with the DCE method based on the EuroQol Valuation Technology (EQ-VT) protocol [17,18] for about 30 countries.

Based on the perspective taken by respondents, valuation of health states could be performed through a hypothetical or experience-based perspective. While value sets have usually been based on members of the general population’s values of health states described to them (hypothetical values), another approach involves individuals in the general population valuing their own current health state (experience-based values) [19-21]. There are also studies where patients valued hypothetical health states [22,23]. A large majority of the value sets have employed a hypothetical perspective [16,17]. Many valuation studies which used an experience-based perspective have also been conducted, including studies in Sweden [24-29]. According to the Dental and Pharmaceutical Benefits Agency in Sweden, the agency that determines state subsidization of a pharmaceutical product, experience-based values are given priority over hypothetical values [30,31]. There is a growing discussion and interest in experience-based perspective in health state valuation, based on general populations’ and patient populations’ valuation of health states globally as shown in different literature [19-21,32-41].

As a health state valuation method, the advantages and possible limitations of VAS have been discussed in comparison to other methods such as TTO and SG. The advantages include being quick to complete and relatively easy for self-administration [42]. However, the above discussed arguments of lack of theoretical basis and not being choice based have also been raised [42,43]. Besides, this idea has been challenged by questioning the need for valuation methods to be based on utility theory [44]. It was pointed out that empirical performance should be used to select the relevant valuation method and VAS valuation was regarded advantageous over other methods in this respect [44]. A recent paper discussed the issue of anchoring at “dead” (ie, to assign 0 to the state of being dead for the calculation of QALYs) and alternative approaches to remedy challenges associated with anchoring at “dead.” The different alternative approaches provided in the paper indicate the potential of VAS to be used in economic evaluation [45].

Some studies comparing VAS with TTO and SG reported the advantage of VAS in terms of feasibility, whereas in other studies it was shown that VAS values differ considerably from TTO and SG values [14,46-52]. Specifically, in terms of feasibility, that is, response rate and cost of administration, findings indicated that VAS performed better than the other methods [14,46-48]. However, correlations of VAS values with those based on the TTO and SG methods were low to moderate, leading the authors to raise concerns regarding the use of VAS in health state valuation [14]. VAS values have also been compared with results from the TTO and DCE methods among patients, professionals, and laypersons. The decision to use VAS or TTO for individual patients and TTO or DCE for laypersons was recommended based on previous findings [49]. Transformation of VAS values to SG and TTO values through power functions has also been explored [50,51]. Concerning this, advise against transformation between VAS values and SG values through power function was expressed due to a lack of theoretical relationships [52]. In short, the studies explored the relationship of VAS with other valuation methods such as TTO and SG, indicating differences in valuations.

EQ VAS, as a component of the EQ-5D instrument, has been used to derive experience-based VAS value sets by using individuals’ overall assessment of their health reported on the EQ VAS to summarize how good or bad the health state they report is. These value sets have been developed in countries such as Sweden, Germany, China, and Canada [24-28]. Applying such value sets, studies reporting population reference values (norms data) and those that compared problems reported on EQ-5D dimensions with EQ VAS values were conducted [53,54]. Furthermore, another study compared patient value sets with that of the general population [55]. In addition, comparisons involving experience-based values developed using patients’ own EQ VAS values across 15 countries indicated significant differences in valuations of the same health states [32]. Similarly, EQ VAS values provided to the same health states by patients with 4 different medical conditions were also found to be different [56]. The cited studies showed the development of value sets based on EQ VAS and their application in addressing different questions in HRQoL research.

EQ VAS as a component of the EQ-5D has been in routine use with its validity and reliability demonstrated in different studies. Specifically, the EQ-5D questionnaire is employed in several Swedish National Quality Registers (NQRs) [57], making it possible to investigate the relationship between EQ-5D health states and self-reported EQ VAS values in different patient populations. As to the routine performance of EQ VAS in clinical settings, its significance as a possible diagnostic tool to predict frailty, the feasibility of its inclusion in daily patient diaries, and its performance in the National Health Service in the United Kingdom have been reported [58-60]. The validity, reliability, and responsiveness of EQ VAS values have also been shown by studies in different countries, including Sweden, in the general population, and in specific patient groups [26,47,61-66].

As shown above, TTO has been employed commonly for health state valuation, while VAS has also been employed in several studies [12,16]. While hypothetical perspectives were used commonly [16], increasing interest in experience-based perspectives was shown [19-21]. VAS has demonstrated advantages over other valuation methods in terms of feasibility [14,46-48]. However, arguments for and against the potential of VAS for use in health states valuation have been forwarded [42-44]. Studies employing EQ VAS in the valuation of health states and in reporting health have been conducted [24-29,53-55]. However, in the context of patient valuations of their own health, there is a knowledge gap in the literature regarding the relationship between the EQ-5D health states and self-assessed EQ VAS values across and within patient populations.

This research project will contribute to addressing the literature gap by adding to the current literature and international debate on the role of EQ VAS as a valuation method for experience-based health states. Addressing this issue will be facilitated through investigating large data sets containing PRO records of different patient populations covering a wide variety of conditions within the 12 Swedish NQRs. Both the EQ-5D-3L and EQ-5D-5L health states will also be investigated.

### Objective

The research project aims to assess EQ VAS as a valuation method with an experience-based perspective through a comparison of its performance across and within patient groups, and with that of the general population in Sweden. The following research questions will be investigated:

How do EQ-5D health states and self-assessed EQ VAS values vary across and within patient groups, and at baseline and 1-year follow-up, and in comparison to the general population data?To what extent do EQ-5D dimensions predict EQ VAS values, and how do the resulting experience-based patient value sets differ when estimated from patients’ data at baseline and 1-year follow-up and how do the EQ VAS values predicted from EQ-5D dimensions differ between different patient groups?How do these patient value sets modeled using data from the registers compare with the Swedish VAS and TTO experience-based EQ-5D value sets obtained from the general population?How do value sets for EQ-5D-3L, derived from EQ VAS, differ from value sets for EQ-5D-5L, derived from its EQ VAS?

## Methods

### Study Design

A longitudinal study involving analyses of data on different patient groups will be conducted by assessing PROs from baseline to 1-year follow-up. The data from patients will be compared with cross-sectional survey data from the general population.

### Data Sources

Data from 12 NQRs on about 700,000 patients with PRO records will be included from the over 1.4 million patients in the registers. Clinical data (age, sex, BMI, diagnosis/es, and interventions) and PROs data (EQ-5D-3L, and EQ-5D-5L) will be retrieved from the registers. Data from cross-sectional population surveys in Sweden will be included for comparison; about 45,000 records were used in developing the Swedish experience-based VAS and TTO value sets [26]. The registers included in the project are described in Tables 1 and 2.

**Table 1 table1:** General information on the 12 National Quality Registers [57,67].

Register	Diagnosis/condition	Intervention^a^	Start year	Unique patients^b^	New entries per year^b^
Better management of patients with Osteoarthritis (BOA)	Hip, knee, hand osteoarthritis	Supported Osteoarthritis Self-Management Programme (SOASP)	2008	110,000	18,000
Swedish Ankle Registry (Swedankle)	Osteoarthritis and inflammatory conditions in the ankle	Total ankle arthroplasty, ankle arthrodesis procedures	1997	4000	400
Swedish National Anterior Cruciate Ligament Register (xBase)	Cruciate ligament injuries	Cruciate ligament surgery	2005	46,000	4000
Swedish Fracture Register (SFR)	All types of fractures including vertebral/spinal fractures	Surgical and nonsurgical treatments	2011	430,000	82,000
Swedish Heart Failure Registry (SwedeHF)	Chronic heart failure	Pharmacological treatment, physical activity	2003	92,000	9500
Swedish Hip Arthroplasty Register (SHAR)	Hip osteoarthritis and other hip joint diagnoses	Hip replacement	1979	370,000	25,000
Swedish Knee Arthroplasty Register (SKAR)	Knee osteoarthritis and other knee joint diagnoses	Knee replacement	1975	220,000	16,000
Swedish National Quality Register for Bipolar Disorder (BipoläR)	Bipolar affective disorder	Pharmacological treatment, patient education	2004	21,000	1500
Swedish National Registry for Respiratory Failure (Swedevox)	Respiratory failure	Long-term oxygen therapy	1987	20,000	1200
Swedish Rheumatology Quality Register (SRQ)	Rheumatic diseases	Medical treatment, rehabilitation	1995	80,000	7000
Swedish Spine Register (Swespine)	Spinal stenosis, disk hernia, and other spinal diagnoses	Spine surgery	1993	130,000	10,000
Swedish Registry for Systematic Psoriasis Treatment (PsoReg)	Psoriasis	Systemic treatment for psoriasis	2007	6500	500

^a^An intervention refers to surgeries or other forms of treatments provided to patients in the registers.

^b^Information on the number of patients and new entries per year was received from registers.

**Table 2 table2:** EQ-5D data collected at the 12 National Quality Registers [57,67].

Register	Follow-up times
Better management of patients with Osteoarthritis (BOA)	First visit, 3 and 12 months; 1, 2, 3, 4, 5, 6, and 7 years after (100 patients per year are randomized to continued follow-ups)
Swedish Ankle Registry (Swedankle)	Before surgery, 6 months, 1 and 2 years after
Swedish National Anterior Cruciate Ligament Register (xBase)	Before surgery, 1, 2, 5, and 10 years after
Swedish Fracture Register (SFR)^a^	A week before injury (recall) and 1 year after
Swedish Heart Failure Registry (SwedeHF)	At new visit, within 6 months and 1 year, once every year
Swedish Hip Arthroplasty Register (SHAR)	Before surgery, 1, 6, and 10 years after
Swedish Knee Arthroplasty Register (SKAR)	Before surgery, 1 year after
Swedish National Quality Register for Bipolar Disorder (BipoläR)	At visit
Swedish National Registry for Respiratory Failure (Swedevox)	At treatment start, 1 year after
Swedish Rheumatology Quality Register (SRQ)	At visit
Swedish Spine Register (Swespine)	Before surgery, 1, 2, 5, and 10 years after
Swedish Registry for Systematic Psoriasis Treatment (PsoReg)	At each revisit due to psoriasis/visit to the skin clinic/telephone conversation with a dermatologist

^a^Baseline data in SFR are collected by a recall of a few weeks after the occurrence of fracture.

### Plan for Data Analyses

The analyses will focus on the 3 main data components coming from the EQ-5D instruments: data collected by the EQ-5D-3L (and EQ-5D-5L for some registers) descriptive systems on the 5 dimensions, the EQ VAS value self-assessed by patients, and indices resulting from transforming the EQ-5D-3L health states into a single index using the Swedish EQ-5D-3L experience-based VAS value sets.

The data from the NQRs will be pooled and diagnoses in each patient group will be used to identify the different subgroups. Records of patients with complete data on age, sex, diagnosis at baseline, and PROs at baseline and 1-year follow-up will be included in the analysis. Although different follow-up times are available in the registers as shown in Table 2, the baseline and 1-year follow-up data will be used in the comparison across the different patient groups. To make comparisons with findings from the patient data, demographic, BMI, and EQ-5D-3L data from the general population survey covering about 50,000 participants will be employed. Detailed information on the general population data is available elsewhere [26].

All analyses will be conducted using SAS version 9.4 (SAS Institute Inc.) and R version 3.6.2 (R Foundation for Statistical Computing).

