### EQ-5D Health States and Observed EQ VAS Values

In addressing the first research question, the proportion of problems (no problem [level 1], some problems [level 2], and severe problems [level 3]) for each dimension and observed EQ VAS values of patients, at baseline and 1-year follow-up, will be compared across and within the patient groups (as well as subgroups based on diagnosis groups) and with the general population data. These descriptive analyses will also be presented by age groups, sex, BMI, and American Society of Anesthesiologists (ASA) physical status classification system (for patient groups with data on ASA class; Tables 1 and 2). Comparison of EQ VAS values by sex in the different patient groups, controlling for age, will be performed using analysis of covariance. Cluster analysis will be performed to assess the distribution of the EQ VAS value in the different patient groups at both baseline and 1-year follow-up.

Furthermore, pooled data from all NQRs will be used to analyze EQ VAS and to explore the influence of both patient characteristics and the patient group (registers). This will be performed by accounting for the grouping of patients by register. Linear mixed effects models with the patient group, preoperative EQ VAS (for the analysis at 1 year and the change from baseline), intervention type, age, and sex as fixed effects, and the patient group as the random effect will be used. Age and sex have been shown to influence EQ VAS values in previous studies [68,69].

Change over time in terms of the proportions of problems reported in each dimension will be presented using the Paretian Classification of Health Change, introduced to apply the Pareto Principle to EQ-5D health states [70]. This analysis will be performed by calculating the proportions of changes in health states from baseline to 1-year follow-up. The changes will be categorized as “no problem” (health state 11111 at both baseline and 1-year follow-up), “no change” (same health state at both baseline and 1-year follow-up), “improved” (improvement in at least one dimension without worsening in any other), “worsened” (worsening in at least one dimension without improvement in any other), and “mixed” (a mix of improvement and worsening) [70]. These changes will be analyzed descriptively in different patient groups and subgroups. In addition, changes in EQ VAS in the Paretian Classification of Health Change categories will be analyzed.

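### Some pooled registers, chiefly BOA with SHAR and SKAR, can contain the same person, yet the pooled models group by register only and BOA's 1-year results may include patients already operated on

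*Protocol article*

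**What the plan says.** Plan for Data Analyses: "The data from the NQRs will be pooled and diagnoses in each patient group will be used to identify the different subgroups". A record enters if age, sex, baseline diagnosis, and baseline and 1-year patient-reported outcomes are complete. The rule sets no condition on membership of another register or on a procedure between the two time points.

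Data Sources, Table 1, gives these diagnoses:

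- BOA: "Hip, knee, hand osteoarthritis", under a self-management programme.
- SHAR: "Hip osteoarthritis and other hip joint diagnoses", under hip replacement.
- SKAR: "Knee osteoarthritis and other knee joint diagnoses", under knee replacement.
- SFR: "All types of fractures including vertebral/spinal fractures".

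Patients are counted as unique register by register. In Table 2, BOA follow-up runs from the first visit and includes a 12-month assessment.

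EQ-5D Health States and Observed EQ VAS Values: the pooled analysis accounts for grouping by register. Its mixed model has intervention type among the fixed effects, and "the patient group as the random effect will be used". No person-level term is named. Value Sets Based on Observed EQ VAS Values adds least-squares and generalized linear models on the pooled data, also without one.

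**The concern.** BOA and the two arthroplasty registers share diagnoses under two kinds of treatment. Someone with hip osteoarthritis can attend the BOA programme and later have the hip replaced. That person then has a baseline and 1-year pair in BOA and another in SHAR. Two consequences follow if the stated plan is applied literally.

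1. **Independence.** The pooled models treat the two pairs as coming from different people.
2. **Attribution.** If the replacement falls between the first BOA visit and the 12-month form, the BOA 1-year EQ VAS, its change from baseline and its Paretian category come after surgery but are reported under BOA. If intervention type is taken from the register of entry, the mixed model also codes the record as self-management.

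The first research question compares health states, EQ VAS and their course over 1 year between patient groups. The second consequence would blur the contrast of BOA with SHAR and SKAR, and sample size does not remove it.

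**Working it through.** The article states no power, alpha or overlap figure. What can be checked is the register counts; beyond that, only assumed ranges are possible.

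**Register counts (Table 1).** 110,000 + 4,000 + 46,000 + 430,000 + 92,000 + 370,000 + 220,000 + 21,000 + 20,000 + 80,000 + 130,000 + 6,500 = 1,529,500. Data Sources says: "Data from 12 NQRs on about 700,000 patients with PRO records will be included from the over 1.4 million patients in the registers". The sum satisfies that lower bound.

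**Ceiling on the BOA overlap.** BOA has 110,000 patients, so at most 110,000 people can be in BOA and also in SHAR or SKAR: 110,000 / 1,529,500 = 7.2% of the Table 1 sum. This is a ceiling, not an estimate. It counts all register patients, not those with complete outcome records.

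**Shift in BOA's mean 1-year change.** Let q be the share of BOA records with a replacement before the 1-year form, and d the difference in mean EQ VAS change between those records and the rest. Compared with BOA without those records, the mean shifts by q × d. Both inputs are assumptions.

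| q | d = 5 | d = 10 | d = 15 | d = 20 |
|---|---|---|---|---|
| 2% | 0.10 | 0.20 | 0.30 | 0.40 |
| 5% | 0.25 | 0.50 | 0.75 | 1.00 |
| 10% | 0.50 | 1.00 | 1.50 | 2.00 |
| 20% | 1.00 | 2.00 | 3.00 | 4.00 |

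**Standard error of a pooled mean.** Let f be the share of records from persons with two records, and ρ the within-person correlation, both assumed. The design effect is 1 + fρ.

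- f = 5%, ρ = 0.3: 1.015, so the true standard error is √1.015 = 1.007 times the reported one.
- f = 30%, ρ = 0.7: 1.21, so √1.21 = 1.10 times.

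This direction holds for pooled means. For a difference between two registers that share people, a positive ρ makes the independence-based standard error too large. The error therefore depends on the quantity reported, which is a reason to model the person and not to apply one correction factor.

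**The case against.** The strongest objection is that this is an omission. Linkage keys and event flags are details that an article commonly leaves to a fuller document, and Ethics Approval and Consent to Participate, which has the pseudonymised data held at one centre, does not rule out linkage. That stands for the missing linkage rule. It does not cover the grouping level: the article states that level, and it is the register.

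Second, the article does not say what BOA does with patients who are operated on. That also stands. A reader might infer that BOA's 1-year result is a post-arthroplasty result; the text supports only that some records can be.

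Third, the study assesses EQ VAS as a valuation method and does not estimate the effect of self-management. This has force for the value sets. Each record pairs a health state with an EQ VAS given at the same time, and a patient who reached that state through surgery still values it validly. A reader might infer biased value-set coefficients, but nothing in the article shows this. The objection does not reach the comparisons of 1-year EQ VAS, change and Paretian categories between groups, which remain stated aims even where they are descriptive.

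Two figures invite over-reading:

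- BOA, SHAR and SKAR together hold 110,000 + 370,000 + 220,000 = 700,000 patients, 46% of the Table 1 sum. That is register size, not overlap.
- The gap between 1,529,500 and the stated total of more than 1.4 million is not evidence of overlap, because the stated total is open-ended and the table counts are rounded.

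Nor do the registers in general follow one disease through its stages. The reading fits BOA with SHAR and SKAR, and even there it is inferred from diagnosis and intervention. Hand osteoarthritis has no matching replacement register. SFR overlap with SHAR or Swespine is only possible, and xBase, SwedeHF, BipoläR, Swedevox and PsoReg do not fit.

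**Conclusion.** The concern holds for a limited set of registers and analyses. Nothing in the stated rules stops one person from contributing to BOA and to SHAR or SKAR, and the stated models would neither account for this nor reveal it. What is exposed is BOA's 1-year, change and Paretian results and their contrasts with the arthroplasty registers and, to a modest degree, the standard errors of the pooled models. Separate analyses within each register are not invalidated merely because a person also appears elsewhere.

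The size is unknown. The shift of 0.1 to 4.0 points and the standard-error factor of 1.007 to 1.10 rest entirely on the assumed q, d, f and ρ. The change is worth making because it is cheap and because the plan as written gives no means of finding out whether the effect is trivial.

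**What to change.** Where the pseudonymised data allow a common person key:

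1. Report the number of persons who appear in more than one register, by pair of registers.
2. Use a person-level random effect or person-clustered variance in the pooled mixed models and the pooled value-set models.
3. Flag BOA records with a SHAR or SKAR procedure between the first visit and the 1-year form. Report BOA 1-year, change and Paretian results with and without them. Label this a sensitivity analysis, since leaving these records out conditions on an event after baseline.

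Do not restrict the pooled analyses to the first episode per person. That would selectively remove the arthroplasty records of people who attended BOA first.

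The cost is a common key and procedure dates from the data holder, plus some data management. No new data collection is needed. If no common key can be supplied, state this as a limitation of the pooled models and of the BOA contrasts.
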